As a summary, it can be said that in order to settle positively in this difficult and changing situation such as the current one, different strategies of action must be developed. Networking is an option, telemedicine techniques are also an option and the combination of both will probably be the optimal way to arrive at a personalized and cost-effective medicine in which all the care links intervene. Our experience allows us to undertake this broad project that aims to manage the entire process of care to the SAHS in a different way and that fits the reality in part related to what is known as the 4 P's of medicine: 1. Personalized (depends on genome characters) 2. Predictive from individual information that can establish predictions 3. Preventive, from predictions implement preventive measures and 4. Participatory by the patient. For the development of this project, the efficiency and cost-effectiveness will be compared between a traditional system and another that basically uses ICTs (Table 1). In order to do so, two options could be chosen: 1) a study only on the "difficult" population (but in this case the behaviour of the high pre-test group would not be known, which could be very different), or 2) which is the one we have chosen, to study all types of patients, without assessing their initial characteristics. We believe that the latter is better because it will be more real and, above all, that in the subsequent analysis the various groups mentioned will already be analyzed.

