**HYPOTHESIS**

1. The efficiency of the management of the SAHS using a work based on TIC's will be optimal to the one currently used in the hospital framework that uses both respiratory polygraph or PSG, including all types of patients from high probability to the most complex.
2. -The cost-effectiveness of the management of SAHS using a work based on ICT's is optimal than that currently used in the hospital framework that uses both respiratory polygraph or PSG, including all types of patients from high probability to the most complex.
3. -Optimal cost-effectiveness will occur especially in complex patients. These patients will directly contact the reference centre which, through the use of ICT, will simplify the process. These same groups of patients when they follow the usual process require several visits at different levels of care and always end up being diagnosed in the referral centers.
4. -The transfer of the telematic process will be possible and can be quickly included in the care routine.

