**OBJECTIVES**

1. -Evaluation of two SAHS management programs, the classic one currently used as opposed to another based on work using ICT's taking the Quebec questionnaire as the main variable and in cases with CPAP the compliance of the treatment.

2. -Analysis of the cost-effectiveness of the programs mentioned above, valuing the Quebec questionnaire as the main variable and, in the cases of CPAP, compliance with treatment.

-Effectiveness of the program based fundamentally on technology between the group of complex patients (Groups 2 and 3 initially described) and the high possibility of suffering from an SAHS (Group 1). Questionnaires: Epworth and EuroQol-5D. Number of complications or side effects. 3. Patient satisfaction questionnaires

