**DESIGN**

DESIGN AND SUBJECTS OF THE STUDY (see figures at the end).

A randomized, open-ended, parallel patient group study in which an analysis of treatment efficacy and cost-effectiveness will be performed. All patients with suspected SAHS diagnosis who belong to the primary care centers (CAP) of the Esquerra del Eixample area of Barcelona, which corresponds to the health area of the Hospital Clínic of Barcelona, will be included consecutively. Patients with: a) psycho-physical incapacity to carry out questionnaires; b) difficulty in using communications technology (smartphone), c) pregnancy, d) failure to obtain informed consent, e) severe or disabling drowsiness or f) unstable illnesses will be excluded. Patients will be randomized, following a sequence generated by a database, into two groups (Table 1):

- Group 1: Patients who follow the usual procedure (hospital). After the visit in the primary physician/specialist out-of-hospital who will make a decisions. Can refer or not the patients to the hospital for a sleep test, titration if appropriate and follow-up for 6-12 months in the hospital (SEPAR regulations).
- Group 2: Telemedicine monitoring by the referral centre: this group of patients will be detected in the outpatient clinic in the same way as group 1 but will carry out the diagnosis, education, treatment and monitoring by means of a totally out-of-hospital telematic procedure carried out by sleep doctors. To minimize possible information biases derived from the open procedure, the professional in charge of introducing and evaluating the questionnaires as well as other main objective variables (measurement of CPAP compliance) will not know the patient's group of belonging.

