**Proceedings:**

Sleep studies and CPAP titration. 1) PSG or hospital respiratory polygraph (PR): The technique and analysis will be carried out according to AASM 2012-SEPAR 2011 regulations. 2) PSG or PR home. The technique and analysis will also conform to the aforementioned standardized regulations. The home care nursing group for chronic patients will also deliver the equipment. In this case the data will be transmitted to the hospital via telematics. For CPAP titration the same procedure will be followed except that the company will provide the automatic equipment for titration, the training will be done from the hospital via telematics and if it is a difficult titration will be adjusted for several days according to results observed telematrically. In the usual treatment arm the professionals of the traditional centres will follow the already established processes. Valid studies for PSG or PR will be considered those that comply with the regulations of the Spanish sleep group. As far as treatment is concerned, the SEPAR regulations will be followed (Lloberes et al. 2011).

Follow-up: Patients will be evaluated according to SEPAR general regulations (onset, at 1, 3 months, and 6 months) and above all depending on the medical criteria. Obviously the extra visits made will be valued. The aforementioned questionnaires will be collected and, in the case of CPAP, compliance at the beginning and at the end (CPAP compliance is not collected in the intermediate months because a group is telematic).

**Justification of sample size.** The main study variable is the change in the score of the dimension of the Quebec questionnaire that requires a higher "n". It is estimated that for an alpha error of 0.05, beta of 0.20 and a clinically relevant difference (change in total score ≥2 points on the questionnaire) between the two study groups, a minimum of 101 patients per randomization arm (202 patients in total) is required. An estimated 20% loss (between those who lose and those who do not tolerate CPAP), according to published data on the degree of compliance with CPAP in Spain is estimated at 75-80%.

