**Effectiveness assessment.**

Statistical analysis shall be based on the intention-to-treat principle. The comparison in the changes in the score of the QUEBEC questionnaire (6 months vs. Basal) between both groups will be carried out from the ANCOVA test, obtaining the mean scores at 6 months for each group adjusted by the basal values and other confusing variables such as the BMI, age or the severity of the SAHS. This test will be performed under the assumption of "least squares". Sub-analysis will be performed with the most complex patients in which the same analysis will be replicated. An analysis per protocol will also be carried out in the case of patients with CPAP depending on whether the compliance is less than or not at 4 h/night. For patients without the last follow-up visit, and therefore only with baseline information, the same baseline value will be imputed to the 24-week visit as it is the most conservative option and against the hypothesis of the potential benefit of CPAP intervention. A significant difference of <0.05 will be established for all tests (SPSS version 20 will be used).

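### No analysis fixed in the protocol can show that the gain is larger in complex patients: the Quebec ANCOVA is only repeated within them, and cost-effectiveness is not analysed by complexity

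*Protocol*

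**What the plan says.** The comparative claim appears in two places in the protocol.

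- Hypothesis, item 3: "Optimal cost-effectiveness will occur especially in complex patients".
- Objectives: "Effectiveness of the program based fundamentally on technology between the group of complex patients (Groups 2 and 3 initially described", continuing to the group with a high probability of SAHS (Group 1).

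The Introduction divides patients into A (high pre-test probability, no comorbidity), B (important associated pathology) and C (low pre-test probability or special populations). It chooses an all-comers design, "to study all types of patients, without assessing their initial characteristics", and adds that "in the subsequent analysis the various groups mentioned will already be analyzed".

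The analysis is set out under Effectiveness assessment. It is an ANCOVA of the Quebec score at 6 months, "adjusted by the basal values and other confusing variables such as the BMI, age or the severity of the SAHS". On subgroups, that section says "Sub-analysis will be performed with the most complex patients in which the same analysis will be replicated". Neither complexity nor its interaction with arm is named as a model term. The Cost-effectiveness section and the secondary objectives after it contain no analysis by complexity. Covariates enter there to reduce uncertainty and through Bayesian model averaging.

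On allocation, the Design section says "Patients will be randomized, following a sequence generated by a database, into two groups". It does not mention complexity.

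**The concern.** To say that something holds especially in one type of patient is to say that the difference between arms is larger in that type than in the others. It takes a contrast of two arm effects to support this. Repeating the between-arm test in complex patients estimates only one of the two. A significant result there is compatible with equal effects, and a non-significant one with a larger effect estimated imprecisely.

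The endpoint does not match either. Hypothesis 3 is about cost-effectiveness, the fixed sub-analysis is about the Quebec score, and the section that deals with cost-effectiveness does not separate patients by complexity.

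A second gap is the time of labelling. The sub-analysis refers to the most complex patients without saying when or from what data they are identified. The Introduction's list of complex cases includes features known only after work-up or treatment, such as poor compliance. Work-up differs by arm: sleep doctors manage the telemedicine group, whereas usual-care physicians may or may not refer for a sleep test. A label applied late could therefore pick out different kinds of patient in the two arms.

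At stake is one of the four hypotheses. The primary comparison in all patients is not affected.

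**Working it through.** **Inputs from the protocol** (Justification of sample size): "for an alpha error of 0.05, beta of 0.20"; a difference of 2 points in total Quebec score; 101 per arm; 20% expected loss.

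**Assumptions, not in the protocol:** two-sided test; the same SD in both groups; complex patients equally frequent in both arms, at 30% to 70% of the sample; normal approximation.

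**Step 1. The plan's own figure.** No SD is stated, so 101 cannot be reproduced independently. Solving for the SD it implies:

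SD = 2 / [(1.960 + 0.842) × √(2/101)] = 5.07

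If the 101 already includes 20% loss (about 81 evaluable), the SD is 4.54. The probabilities below are the same under either reading, because in each case the SD is set so that overall power is 80%.

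**Step 2. The complex-only test when the effects are equal.** Let the true effect be 2 points in both groups, so that no group benefits especially. With f the complex share:

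SE(complex) = 5.07 × √(2/(101f)); P(significant) = Φ(2/SE − 1.960)

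At f = 0.5 there are 50.5 per arm, SE = 1.01 and P = 0.51.

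**Step 3. Separate tests in both groups.** The chance of significance in complex patients but not in the others is P(complex) × [1 − P(others)]. At f = 0.5 this is 0.508 × 0.492 = 0.25.

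**Step 4. The interaction.** SE(interaction) = √[SE(complex)² + SE(others)²]. At f = 0.5 this is √2 × 1.01 = 1.43. The difference in effects detectable with 80% power is 2.802 × 1.43 = 4.0 points.

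| Complex share | P(complex significant), equal effects | P(significant in complex only), equal effects | Interaction power, 2-point difference | Difference detectable with 80% power |
|---|---|---|---|---|
| 30% | 0.34 | 0.12 | 0.25 | 4.4 |
| 50% | 0.51 | 0.25 | 0.29 | 4.0 |
| 60% | 0.58 | 0.34 | 0.28 | 4.1 |
| 70% | 0.65 | 0.43 | 0.25 | 4.4 |

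For 80% power at a 2-point difference in effects, the trial would need about 4 × 101 = 404 per arm at an even split, and about 481 at 30:70.

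These figures are for the Quebec score. The protocol gives no variance for cost or net benefit, so no equivalent figure can be derived for the quantity in hypothesis 3.

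**The case against.** Several points on the other side have force.

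- **The sub-analysis is not said to test hypothesis 3.** This is true, and the protocol nowhere says that significance in complex patients will be taken as superiority there. A reader might infer that it does; the text does not support this. What remains is that no other stated analysis addresses the hypothesis.
- **The other groups will be analysed too.** The Introduction does promise this, so a reader would be wrong to infer that high-probability patients are ignored. But no contrast between groups is named, and separate tests do not supply one (step 3).
- **Entry characteristics are assessed.** A reader might infer from "to study all types of patients, without assessing their initial characteristics" that they are not. In context the phrase explains why patients are not selected by type. The Variables section collects clinical data, symptoms of other sleep disorders and examination findings in all included patients. Groups A to C rest largely on features that need no sleep test. A baseline label is therefore feasible; the protocol simply does not require one. That a late label would differ between arms is a risk arising from this silence, not something the protocol plans.
- **The objective is ambiguous.** A reader might take it as comparing patient types within the telemedicine arm, which would not be a randomised contrast. It can equally mean the programme's effect against usual care in each type. The wording does not settle this.
- **Interaction terms often belong in the SAP.** They do, and one may exist that supplies the contrast. But the protocol itself fixes a complex-only repeat, and a SAP that follows it faithfully would inherit the mismatch.
- **The interaction test is weak.** This stands, and it limits what the remedy can deliver.

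**Conclusion.** The point holds in a limited form. The protocol makes a comparative claim about complex patients and fixes no analysis able to support it: the Quebec ANCOVA is repeated within one subgroup, and cost-effectiveness is not examined by complexity. With an equal 2-point effect in both groups, the complex-only test would be significant about 34% to 65% of the time. This rests on the back-solved SD of about 5.07, a two-sided test, a common SD and a complex share of 30% to 70%. None of these is stated in the protocol.

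The label's timing is a secondary weakness: it is left open, and some of the features listed as complex arise after randomisation. The documents do not show that patients will in fact be labelled late, or that subgroup significance will be misread. The change should be made, but the main comparison does not depend on it.

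**What to change.** 1. Define complex (groups B and C of the Introduction) and high-probability (group A) from data recorded before randomisation. Exclude features that emerge from work-up or treatment. Use the A/B/C labels throughout, because the numbers in the Objectives clash with the names of the trial arms.
2. Replace the complex-only repeat with an arm-by-group interaction in the ANCOVA on all patients. Report the Quebec effect in each group, with the difference and its interval.
3. Report the incremental net benefit in each group in the same way, with the difference and its interval, since this is the quantity in hypothesis 3.
4. Label the analysis exploratory and state its power: about 25% to 29% for a 2-point difference in effects, and about 80% for 4.0 to 4.4 points.

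Stratifying the randomisation by group is optional; a label fixed at baseline is enough for a valid subgroup comparison.

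The cost is one baseline field, modest extra modelling (more in the Bayesian cost-effectiveness model than in the ANCOVA), and a weaker statement about hypothesis 3 than its present wording suggests.

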**Cost-effectiveness**:

The costs generated by both protocols will be evaluated against the effectiveness of the main variable Quebec, also as secondary (Epworth and EuroQol-5D), using Bayesian cost-effectiveness analysis techniques. Bayesian techniques are especially suitable for this project where the experience of the decision-maker can be incorporated into the study by means of an a priori probability distribution that adequately reflects his or her judgments on the variables studied. In addition, we will avoid the usual assumptions of normal costs and we will be able to use asymmetric costs closer to real practice. This will lead us to the use of Markov Chain Monte Carlo (MCMC) techniques for the simulation of the measures of interest: the cost-effectiveness ratio of each treatment, the incremental cost-effectiveness ratio (ICER), he cost-effectiveness plan, the the net benefit of each treatment, the incremental net benefit (NB) and the cost-effectiveness acceptability curve. Each of these measures has its natural interpretation in terms of the probability and willingness to pay of the decision-maker in the face of an increase in the patient's state of health, making them especially attractive due to their practical applicability. The statistical-mathematical process is not simple, but in this project, we will design a set of codes of easy computer implementation in such a way that the decision-maker obtains in an easy and simple way these measures of interest for later decision making (17).

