Secondary objectives: Comparison between both arms of the cited questionnaires (Epworth, EuroQol-5D, Satisfaction and number of side effects). In addition to having other variables of interest collected from each patient, these variables may act as covariates that help minimize uncertainty in the estimation of effectiveness and incremental cost. We therefore propose a series of secondary objectives linked to the proposed Bayesian methodology: 1) to develop a cost-effectiveness for more than one measure of effectiveness, also proposing clear decision-making measures that are easy to interpret and 2) to develop a BMA model (Bayesian Model Averaging) for estimating cost-effectiveness. The BMA solution is obtained as an average of the coefficients obtained by all the possible combinations of the covariates weighted by the a posteriori probability of each model. This implies the selection of which variables have predictive capacity since the choice of a single model among all the possible ones does not consider the uncertainty associated with the choice of the correct model. This objective will allow us to innovate this type of study since we will automatically select the relevant variables by means of the Bayesian selection of covariates (17).

Logistics: a) Protocol: based on the present memory; b) Procedure notebook: explains step by step the development of the study and contains all the questionnaires, tests and how to carry them out for standardization, c) Data collection notebook containing the variables to be collected distributed in the visits. The order and form is the same as that of the database; d) Database with domain belonging to the requesting centre.

Ethical aspects: The study will be carried out in accordance with the guidelines and principles of the Declaration of Helsinki and will be approved by the Ethics and Clinical Research Committee. All study subjects will provide informed consent in writing prior to participation. The quality assurance procedure will be permanent (data management, data security procedures are sufficient, effective and well documented).

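### Hypothesis 3 expects the advantage of telemedicine to be greatest in complex patients, but no stated analysis compares the between-arm effect across patient types

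*Protocol*

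**What the plan says.** Five parts of the protocol bear on patient type.

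- **Hypothesis, item 3:** "Optimal cost-effectiveness will occur especially in complex patients".
- **Introduction, closing paragraph:** a study of difficult patients only is rejected because it would leave the high pre-test group unknown. All types are enrolled instead, and "in the subsequent analysis the various groups mentioned will already be analyzed". No method is given.
- **Objectives:** "Effectiveness of the program based fundamentally on technology between the group of complex patients", set against those with a high probability of SAHS. The hospital arm is not mentioned.
- **Effectiveness assessment:** the between-arm ANCOVA of Quebec change, followed by "Sub-analysis will be performed with the most complex patients in which the same analysis will be replicated". Neither a parallel analysis in typical patients nor an arm-by-group term is stated.
- **Cost-effectiveness, and the secondary objectives after it:** "The costs generated by both protocols will be evaluated against the effectiveness of the main variable Quebec". This is a comparison of the two programmes as wholes. Other patient variables enter because "these variables may act as covariates that help minimize uncertainty in the estimation of effectiveness and incremental cost", and for model averaging. Complexity is not named.

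**The concern.** The word *especially* in hypothesis 3 makes it a claim of effect modification: the telemedicine-versus-hospital contrast should be larger in complex than in typical patients. Only a comparison of the two between-arm effects can support or weaken that claim, and no stated analysis makes it.

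- The replicated ANCOVA gives one of the two effects and nothing to set it against.
- The natural reading of the objective compares patient types inside the telemedicine programme. Randomisation does not protect that contrast. Complex and typical patients may differ in prognosis and in room to improve under any programme.
- The outcome does not match. The hypothesis is about cost-effectiveness, while the replicated analysis is about the Quebec score.

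At stake is the answer to one of four numbered hypotheses. The design choice is at stake too: all patient types were enrolled so that the high pre-test group would not be left unknown, yet the one subgroup analysis that is specified leaves that group out.

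**Working it through.** **Inputs.** From Justification of sample size: "for an alpha error of 0.05, beta of 0.20 and a clinically relevant difference" of 2 points, with 101 patients per arm. Assumed, because the protocol is silent: a two-sided test, equal variance in both patient groups, the same mix of patients in each arm, and a complex share *f*. The main range for *f* is 40–60%, with 25% and 75% as a wider check.

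**Step 1: the plan's own figure.** No standard deviation is stated, so 101 per arm cannot be reproduced independently. Solving backwards:

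SD = 2 / [(1.960 + 0.842) × √(2/101)] = 5.07.

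If 101 already includes the 20% loss (101 × 0.8 = 80.8 evaluable), the implied SD is 4.54. In either case the standard error of the overall arm difference implied by 80% power is the same: 2 / 2.802 = 0.714. The steps below need only this value.

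**Step 2: the replicated analysis when nothing differs.** Let the true effect be 2 points in every patient. The standard error in the complex group is 0.714/√f, so

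power = Φ(2.802 × √f − 1.960).

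For f = 0.5: Φ(1.981 − 1.960) = Φ(0.021) = 51%.

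**Step 3: the contrast that hypothesis 3 needs, on the Quebec scale.**

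SE of the difference in effects = √(0.714²/f + 0.714²/(1−f)) = 0.714 / √(f(1−f)).

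For f = 0.5: 0.714 / 0.5 = 1.43. The 95% half-width is 1.960 × 1.43 = 2.80. The difference detectable with 80% power is 2.802 × 1.43 = 4.0. Power for a 2-point difference is Φ(2/1.43 − 1.960) = 29%.

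| Complex share (assumed) | Complex-only test significant, same 2-point effect in all | SE of difference in effects | 95% half-width | Difference detectable at 80% power | Power for a 2-point difference |
|---|---|---|---|---|---|
| 25% | 29% | 1.65 | 3.23 | 4.62 | 23% |
| 40% | 43% | 1.46 | 2.86 | 4.08 | 28% |
| 50% | 51% | 1.43 | 2.80 | 4.00 | 29% |
| 60% | 58% | 1.46 | 2.86 | 4.08 | 28% |
| 75% | 68% | 1.65 | 3.23 | 4.62 | 23% |

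The second column rises and falls with the size of the complex group and carries no information about a difference in effect.

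**Step 4: cost-effectiveness.** The protocol gives no cost figures, so the precision of a net-benefit contrast between groups cannot be computed.

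**The case against.** **The unseen analysis plan.** A statistical analysis plan may add an interaction term or cost-effectiveness by subgroup, and the Introduction announces that the various groups will be analysed. This has weight: the silence in Cost-effectiveness alone would be missing detail. But Effectiveness assessment goes further and names a subgroup method, and that method cannot answer hypothesis 3.

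**The replicated ANCOVA is sound in itself.** It is a randomised contrast and validly estimates the effect in complex patients. This stands; the defect is that it is not enough for the claim made.

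**A stronger reading.** A reader might infer that the trial would declare hypothesis 3 confirmed or refuted on the complex-only p-value. The protocol states no such rule. The 0.05 level is set for all tests, but nowhere is this test tied to hypothesis 3. A reader might also count how often one group would be significant and the other not. That needs a separate test in typical patients, which the protocol does not state. The probabilities in the second column of the table therefore illustrate why a single-group result is uninformative; they are not error rates of the plan.

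**The objective is an ambiguous fragment.** Since effectiveness is elsewhere defined between arms, it could mean comparing the programme effect across patient types. The within-programme reading is more natural but not certain, which argues for rewording and not for calling the objective invalid.

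**Low precision.** The interaction is poorly estimated at this sample size. That is true and limits what can be gained, but it does not make a single-group result evidence of a difference.

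**Conclusion.** The concern holds as a mismatch between a numbered hypothesis and the analyses stated. Hypothesis 3 claims a difference in effect between patient types; the protocol fixes an estimate in one type, on a different outcome, and states no cost-effectiveness analysis by complexity. A direct comparison is available at little cost. With the plan's own figures and an assumed complex share of 40–60%, its 95% interval on the Quebec scale is about ±2.8 to 2.9 points, and 80% power exists only for a difference of about 4 points. It can therefore only be exploratory.

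These figures assume a two-sided 0.05 test and that the stated 80% power is achieved. The case that no interaction is stated rests on the text alone and needs none of these assumptions. Severity is moderate: the primary Quebec comparison and the overall cost-effectiveness analysis stand as they are.

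**What to change.** 1. **Effectiveness assessment.** Replace the complex-only ANCOVA with one ANCOVA in all randomised patients: arm, baseline Quebec, the other planned covariates, patient group, and arm × group. Report the arm effect in each group and the difference between them with its 95% confidence interval.
2. **Patient group.** Define it as A versus B/C of the Introduction, recorded at entry from the baseline clinical data, and tie the phrase about the most complex patients to that definition. The Objectives number these groups 1 to 3, while the Design section uses Groups 1 and 2 for the arms, so the labels should be aligned.
3. **Cost-effectiveness.** Report incremental net benefit in each patient group and the posterior distribution of the difference.
4. **Objectives.** Reword the fragment as the difference between patient types in the telemedicine-minus-hospital effect.
5. **Interpretation.** State that only this difference bears on hypothesis 3, that it is exploratory, and how imprecise it is expected to be.

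**Cost.** No extra patients or visits. It does need one extra baseline classification: the Variables section lists no such variable, and the Introduction says that patients are taken without regard to their initial characteristics. It also adds some Bayesian analysis, and hypothesis 3 will then rest on an imprecise estimate.

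### Carrying the baseline Quebec score forward is justified as conservative against a CPAP benefit, but that does not make it conservative for telemedicine versus hospital care

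*Protocol*

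**What the plan says.** The Effectiveness assessment section of the protocol sets the primary analysis: an ANCOVA of the Quebec questionnaire, "obtaining the mean scores at 6 months for each group adjusted by the basal values" and other covariates. It adds that "Statistical analysis shall be based on the intention-to-treat principle".

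The same section fixes the missing-data rule. "For patients without the last follow-up visit, and therefore only with baseline information", it says, "the same baseline value will be imputed to the 24-week visit as it is the most conservative option". The reason given is that the rule goes "against the hypothesis of the potential benefit of CPAP intervention".

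The Design section describes a different contrast. In Group 1, the out-of-hospital physician decides on the usual pathway: "Can refer or not the patients to the hospital for a sleep test, titration if appropriate". Group 2 "will carry out the diagnosis, education, treatment and monitoring by means of a totally out-of-hospital telematic procedure carried out by sleep doctors". The Proceedings section covers CPAP titration under both pathways. The Summary gives the working premise as a 2-point advantage for the telematic group.

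The sample-size paragraph expects 20% loss, pooled over arms, and counts patients who do not tolerate CPAP within it.

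**The concern.** Setting a lost patient's change to zero is conservative in a trial of CPAP against no CPAP, where improvement is expected mainly in the treated arm. Here both arms can receive CPAP and patients in both may improve. The rule removes improvement from each arm in proportion to that arm's loss. Its effect on the difference therefore depends on which arm loses more patients, and nothing in the rule makes that work against telemedicine.

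At stake is the primary result. With unequal loss, the ANCOVA could show an arm difference that does not exist, in either direction, or hide a real one. The protocol's wording would lead a reader to treat a positive result as protected against this.

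**Working it through.** **Inputs from the protocol.** 101 patients per arm, alpha 0.05, power 0.80, target difference 2 points, pooled loss 20%. No SD, no expected gain and no loss by arm are given, and alpha is not stated as one- or two-sided. I take it as two-sided.

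**The plan's own figure.** The 101 per arm cannot be reproduced without an SD, so I solved for it: SD = 2 × √(n / (2 × (1.960 + 0.842)²)).
- n = 101 with no allowance for loss: SD = 5.07.
- n = 101 already including 20% loss, so 101 × 0.8 = 80.8 evaluable: SD = 4.54.

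I use 4.54 to 5.07 as the assumed range.

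**Expected difference under the rule.** Let pT and pH be the proportions missing the final visit, M the true mean gain in the hospital arm and δ the true telemedicine advantage, with loss unrelated to outcome. Then

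expected estimate = (M + δ)(1 − pT) − M(1 − pH)

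and

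bias = M(pH − pT) − δ·pT.

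**No true difference (δ = 0).** The bias is M(pH − pT), towards the arm that loses fewer.

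| Loss, telemedicine / hospital | Bias | M = 4 | M = 8 |
|---|---|---|---|
| 20% / 20% | 0 | 0 | 0 |
| 15% / 25% | 0.1M | +0.4 | +0.8 |
| 10% / 30% | 0.2M | +0.8 | +1.6 |
| 30% / 10% | −0.2M | −0.8 | −1.6 |

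**Type I error.** I simulated 4,000 trials of 101 per arm with baseline-adjusted ANCOVA, loss unrelated to outcome, and change independent of baseline. The entries are rates of falsely favouring telemedicine, against a nominal 2.5% in that direction.

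| Loss, telemedicine / hospital | M = 4, SD 4.54 / 5.07 | M = 8, SD 4.54 / 5.07 |
|---|---|---|
| 15% / 25% | 10% / 8% | 19% / 18% |
| 10% / 30% | 26% / 23% | 59% / 54% |

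With 20% loss in both arms, the two-sided rate stayed at about 5%. With 30% / 10%, the errors favoured hospital care at rates close to the 10% / 30% row (for SD 4.54, 26% and 60%). A variant with SD 5.0 and baseline correlation 0.5 gave two-sided rates of 12% (M = 5) and 20% (M = 8) at 15% / 25%, and 36% and 61% at 10% / 30%. Together the runs span about 8–20% and 23–61%.

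**True difference of 2 points, M = 4.**
- 20% / 20%: 6 × 0.8 − 4 × 0.8 = 1.6. Simulated power at SD 4.54 is 70%, against 80% for complete cases.
- 18% / 20%: 6 × 0.82 − 4 × 0.8 = 1.72.
- 10% / 30%: 6 × 0.9 − 4 × 0.7 = 2.6.
- 30% / 10%: 6 × 0.7 − 4 × 0.9 = 0.6.

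The rule is therefore conservative for telemedicine superiority when loss is equal or higher in the telemedicine arm, or when any excess hospital loss is small enough that M(pH − pT) ≤ δ·pT.

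**How many patients.** 20% of 202 is 40.4. Because the 20% also counts CPAP intolerance, and an intolerant patient who attends at 6 months has an observed score, about 40 is an upper bound on missing final visits if the protocol's estimate is right.

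**The case against.** The strongest defence is that the rule may be harmless, or even right. The protocol gives one pooled loss figure and forecasts no imbalance. With equal loss the estimate is pulled towards zero, which is conservative for a superiority claim. If patients who drop out really stay at baseline, as those who abandon treatment may, baseline imputation is unbiased in the mean and complete-case analysis is not. With equal true arm means m and 15% / 25% loss, completer means would be m/0.85 and m/0.75, a spurious difference of 0.16m favouring hospital care. Multiple imputation under missing at random could inherit that error. All of this stands. It limits the size of the point and shapes the remedy, but it does not make the stated reason apply to the randomised contrast.

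A reader might also infer three stronger things that the protocol does not support:
- **That the hospital arm will lose more patients, so the rule favours the trial's own hypothesis.** The text on optional referral describes the usual-care strategy. It does not say that non-referred patients miss the 6-month assessment.
- **That the rule contradicts the visit schedule.** The follow-up text says "Patients will be evaluated according to SEPAR general regulations (onset, at 1, 3 months, and 6 months", but its sentence on collecting questionnaires can be read as start and end only. Whether Quebec scores exist at 1 and 3 months is unclear, so no contradiction is shown.
- **That the false-positive rates above are expected behaviour.** They hold only for the assumed imbalance and gain.

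Sensitivity analyses may be set out in the SAP, so their absence from the protocol is not held against it. The rule and its rationale, however, are fixed in the protocol itself.

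**Conclusion.** The point holds in a conditional form. The protocol fixes a single-imputation rule for the primary outcome and defends it with a property that applies to a CPAP comparison. For telemedicine versus hospital care that property is not guaranteed. Bias under no true difference requires both unequal loss and a non-zero mean gain among lost patients; it is then M(pH − pT), or 0.4 to 1.6 points in the hospital-heavier scenarios shown, against a 2-point target. With equal 20% missingness the cost is attenuation from 2 to 1.6 and no inflation of type I error. The losses by arm, gains and SDs are assumptions. It would go too far to say that the rule biases the trial, or in which direction. This should be fixed before analysis, but it does not invalidate the design.

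**What to change.** 1. Delete the statement that baseline imputation is the conservative choice, together with its CPAP rationale.
2. Make the primary analysis the planned ANCOVA after multiple imputation of the 6-month Quebec score, done separately by arm. Use baseline Quebec, age, BMI, SAHS severity or pre-test group, and the 1- and 3-month Quebec scores if they are collected.
3. Keep baseline imputation as a sensitivity analysis. Add a tipping-point analysis that varies the assumed outcome of lost patients by arm, because missing at random may fail if dropouts stay at baseline.
4. State whether the Quebec questionnaire is collected at 1 and 3 months. If it is, correct the premise that patients without a final visit have baseline data alone.

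The cost is one revised paragraph and a little more programming, with no new data. The downside is that the primary analysis then rests on missing at random, which is why the tipping-point analysis must accompany it.
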